## Abstract

**Background:**

Past studies have found that children with Developmental Coordination Disorder (DCD) engage in less physical activity than typically developing children. This “activity deficit” may result in children with DCD being less physically fit and more likely to be overweight or obese, potentially increasing later risk for poor cardiovascular health. Unfortunately, the majority of DCD research has been limited to cross-sectional designs, leading to questions about the complex relationship among motor ability, inactivity and health-related fitness. Of the few longitudinal studies on the topic, determining precedence amongst these factors is difficult because study cohorts typically focus on mid to late childhood. By this age, both decreased physical fitness and obesity are often established. The Coordination and Activity Tracking in CHildren (CATCH) study will examine the pathways connecting DCD, physical activity, physical fitness, and body composition from early to middle childhood.

**Methods:**

The CATCH study is a prospective cohort study. We aim to recruit a cohort of 600 children aged 4 to 5 years (300 probable DCD [pDCD] and 300 controls) and test them once a year for 4 years. At Phase 1 of baseline testing, we assess motor skills, cognitive ability (IQ), basic anthropometry, flexibility and lower body muscle strength, while parents complete an interview and questionnaires regarding family demographics, their child’s physical activity, and behavioural characteristics. Children who move on to Phase 2 (longitudinal cohort) have their body fat percentage, foot structure, aerobic and anaerobic fitness assessed. An accelerometer to measure physical activity is then given to the child and interested family members. The family also receives an accelerometer logbook and 3-day food dairy. At years 2 to 4, children in the longitudinal cohort will have all baseline assessments repeated (excluding the IQ test), and complete an additional measure of perceived self-efficacy. Parents will complete an ADHD index twice within the follow-up period. To assess the association between DCD, fitness and adiposity, our primary analysis will involve longitudinal growth models with fixed effects.

**Discussion:**

The CATCH study will provide a clearer understanding of pathways between DCD and health-related fitness necessary to determine the types of interventions children with DCD require.

## Background

Developmental coordination disorder (DCD) is a prevalent and serious neuro-developmental condition characterized by problems with fine and/or gross motor coordination that result in impairment in everyday functioning, play, and academic achievement [1, 2]. On average, DCD affects 1 to 2 children in each classroom [3]. Although there are clear diagnostic criteria [1, 4], DCD is seldom recognized or diagnosed [5]. As a result, the difficulties experienced by children at school and at home are often mistakenly ascribed to oppositional behaviour, learning or attention difficulties, or simple laziness [5, 6].

In addition to academic and self-care difficulties, children with DCD have repeatedly been shown to be less physically active than other children [7, 8]. One hypothesis in the field is that because of this “activity deficit” [9], children with DCD become less physically fit than typically developing children and are more likely to be overweight or obese [10, 11]. If true, this poses a serious problem for children with DCD, because they would be at a greatly increased risk for poor cardiovascular health and, in the long term, for early onset of chronic disease [12]. In addition, recent evidence of a link between inactivity and delayed skeletal development has now also raised concern about other potential health consequences, such as increased risk of fractures and injuries [13]. Testing the idea of an activity deficit also has the potential to clarify what types of interventions might be most appropriate for these children.

To date, most research on physical health and DCD has used cross-sectional study designs and has therefore not examined the complex associations among DCD, inactivity and health-related fitness over time [14–18]. At best, cross-sectional studies can only suggest causal associations among DCD, physical activity, physical fitness, and obesity. Among the few studies that have used longitudinal designs [19–21], determining the precedence of each of these factors has been complicated by the fact that data collection started in middle childhood (ages 8 years and older). By this age, both decreased physical fitness and obesity are often established [20–22]. Another limitation of previous longitudinal research is that motor coordination has been assessed at only one time using a single motor test *and* without considering other diagnostic criteria [19–21]. While the motor impairments that are at the core of DCD are believed to be stable and chronic, this is a largely untested assumption. Poor motor skill development may lead to withdrawal from physical activity and subsequently, to decreased fitness and overweight/obesity, conditions that are potentially amenable to change. However, it is equally plausible that low strength and endurance, and even obesity, could be features of the developmental syndrome that inevitably emerge over time.

The goal of the Coordination and Activity Tracking in CHildren (CATCH) study is to examine the pathways connecting DCD, physical activity, physical fitness, and body composition from early to middle childhood. These relationships are important in order to determine the types of interventions children with DCD require. This prospective cohort study will follow 4- and 5-year old boys and girls for 4 years with annual assessments of physical activity, body composition, health-related fitness, and motor skills.

Specifically, our objectives are:To examine the stability of DCD over time. We hypothesize that children who meet study criteria for DCD at baseline will continue to meet criteria for DCD at follow-up assessments, and that children who do not meet study criteria for DCD at baseline will not meet criteria in later assessments.To evaluate the precedence of DCD, fitness and adiposity. We hypothesize that children who meet criteria for DCD at baseline will, over time, show decreasing aerobic and anaerobic fitness and increasing weight (Body Mass Index [BMI], body fat percentage and waist circumference) relative to children who are typically developing. This divergence will be partially mediated by differences in physical activity.

## Methods/Design

### Study design

The CATCH study is a prospective cohort study with an initial cohort of 600 children aged 4 or 5 years at baseline: 300 with probable DCD (pDCD) and 300 controls. Using the Optimal Design software package [23], we have determined that an analysis with two groups of 300 assessed on 4 occasions will permit the detection of standardized effect size differences of approximately 0.3 with 80 % power and a significance level of 0.05. Taking expected attrition into account (~10 % per year), standardized effect sizes above approximately 0.35 will remain detectable. This means with 600 participants, we will be adequately powered to detect modest effect size differences between our two groups while accounting for loss to follow-up over time. The control group is randomly selected from the children completing the laboratory assessment who do not meet criteria for DCD. Data collection occurs at annual study visits, which include a motor coordination assessment, anthropometric assessments, and non-invasive physical fitness measures. All measures have previously been conducted successfully in this age group [24–26].

Through a parental interview, DCD questionnaire and demographic survey, parents provide additional information about their child’s performance of daily motor activities, demographics, measures of health and risk factors for obesity (adapted from surveys exploring these risk factors) and measures of participation in physical activity [27, 28]. The Hamilton Integrated Research Ethics Board has provided ethical approval for the study*.*

### Participants

The target age range for participants is 48 months, 0 days to 71 months, 30 days at study entry. Children with a physical disability or diagnosed medical condition that affects motor coordination (e.g. Cerebral Palsy) are excluded from the study. Children with a birth weight lower than 1500 g are also not eligible. These eligibility criteria are necessary in order to rule out medical conditions other than DCD, which may be responsible for poor motor coordination.

#### Recruitment strategy

The sample is drawn from various community organizations and sites within the city of Hamilton, Ontario and surrounding area. These include parenting resource and support centres (e.g. Ontario Early Years Centres, Best Start programs), kindergarten classes in the public and Catholic school boards, among others.

Parents who provide their contact information via partnering community sites or contact the study team directly are telephoned by the research staff to determine their child’s eligibility and obtain informed, verbal consent. Eligible parents and children who provide verbal consent are invited to participate in the Phase 1 baseline laboratory visit. The recruitment process involves one randomization to select a proportion of Movement Assessment Battery for Children (M-ABC-2)-negative (typically developing) children into the control arm in the longitudinal study.

After Phase 1 of baseline testing, all children positive on the M-ABC-2 (pDCD) are recruited to the longitudinal study. Children who are negative on the M-ABC-2 are randomized to determine if they will continue onto Phase 2 (Fig. 1). Randomization probabilities are calculated to produce a sample of controls with a distribution of motor functioning that matches the population distribution of non-cases.

**Fig. 1 Fig1:**
[figure not shown]
Recruitment and study protocol. ADHD, Attention Deficit Hyperactivity Disorder; DCD-Q, Developmental Coordination Disorder Questionnaire; KBIT-2, The Kaufman Brief Intelligence Test 2^nd^ Edition; M-ABC-2, Movement Assessment Battery for Children 2^nd^ Edition; CBCL, Child Behaviour Checklist; PEGS, Perceived Efficacy and Goal Setting System

#### Assembling the study cohort at baseline

As noted previously, we will assemble a cohort of 600 children for the longitudinal portion of the study: 300 children meeting criteria for pDCD (see below) and 300 typically developing children. This approach will provide a balanced sample, which maximizes statistical power at a given sample size. We will use random sampling rather than matching because this approach ensures that this group is representative of typically developing children with respect to both measured and unmeasured variables [29].

#### Defining cases of pDCD

We will define cases based, in part, on the 2011 European Academy of Childhood Disability (EACD) Guidelines for Identification of Children with DCD [30], which require: (1) a score at or below the 16^th^ percentile on a standardized measure of motor impairment (M-ABC-2) [31]; (2) evidence of impact on daily function; (3) IQ score above 70 (KBIT-2) [32]; (4) absence of any medical condition affecting motor functioning (parent reported). In addition, we have also decided to exclude children whose birth weight is less than 1500 grams, as children with very low birth weight are apt to present with a variety of co-morbid health problems that may affect motor coordination. The EACD guidelines also recommend repeated measurement of motor function in children under 6 years of age to ensure valid and reliable identification of children with DCD, which we will also do.

### Measurements

#### Motor coordination

A standardized motor coordination assessment is conducted in order to identify children with pDCD. We are using the Movement Assessment Battery for Children 2^nd^ Edition (M-ABC-2), the most widely used assessment for the identification of DCD [26, 33, 34]. The M-ABC-2 is an individually administered standardized test which includes 8 motor tasks within 3 categories: Manual Dexterity; Aiming & Catching; and Balance (static and dynamic). Raw scores on these items are converted into standard scores based on the child’s age, and then converted into an overall percentile. Test-retest reliability and standard of error of measurement for the total test scores have been reported to be 0.80 and 1.34, respectively [31]. Studies have shown that the M-ABC-2 is a reliable and valid tool for the assessment of movement difficulties, even in very young children (4 to 6 years of age) [31].

#### Performance of daily activities

Questionnaires to assess the impact of DCD on everyday activities have not yet been validated for this age. Therefore, a published parental semi-structured interview (developed by our team) is used to ask parents how their child’s motor coordination difficulties affect active play, self-care, and time spent at pre-school/school. It has been used successfully in studies with children 4 years and older to confirm DCD [35, 36]. The interview is also administered to parents of typically developing children. For a child to be considered to have DCD, parents must report evidence of significant functional impact in at least one domain (e.g. self-care).

#### Intellectual ability

The Kaufman Brief Intelligence Test 2^nd^ Edition (KBIT-2) is administered only at baseline. This is to ensure all children included in the study have IQs > 70. It is a standardized measure of intelligence that has been used in large studies to estimate children’s cognitive ability. The KBIT-2 measures function in two cognitive domains (verbal and non-verbal) and is a reliable measure that requires no reading or writing and is suitable for children 4 years of age and older [37].

#### Body composition analysis

Basic anthropometric assessments are conducted. Standing and sitting height are measured without shoes to the nearest 0.1 cm using a calibrated portable stadiometer (Seca 213) and body mass is measured in light clothing without shoes to the nearest 0.1 kg using a digital scale (Seca 869). From this, BMI can be calculated. In order to assess body fat distribution, specifically central adiposity, waist circumference (WC) is measured to the nearest 0.1 cm at 2 sites (the uppermost lateral border of the iliac crest, and the midpoint between the last floating rib and the top of the iliac crest) [38]. WC has been shown to correlate well (*r* = 0.84) [39–41] with trunk fat mass measured by duel-energy x-ray absorptiometry and to be a sensitive marker of future cardiovascular risk in young children [42]. If the two height and weight measures differ by more than 0.1 cm (0.4 cm for sitting height) or 0.1 kg, additional measures are taken until there are two that differ by ≤0.1 cm (0.4 cm for sitting height) or ≤0.1 kg, respectively. If the two WC measures differ by more than 0.5 cm, additional measures are taken until there are two that differ by ≤0.5 cm. The average of the two closest measures is used for height, weight and WC. Body composition is also assessed using bioelectrical impedance analysis (BIA) (RJL Systems – Quantum IV Body Composition Analyzer) while the child is in a supine position. BIA is a simple, non-invasive method to estimate percent body fat by passing a low level electrical current through the body [43]. Fat-free mass (FFM) will be calculated using an age-specific equation [44] validated against the doubly-labelled water technique. Percent body fat is then calculated as [(Body weight – FFM)/body weight] ×100.

#### Foot structure

Previous work examining the relationships between foot structure, balance and weight in children has found differences between obese and non-obese children. Children who are obese have flatter feet [45, 46] than do children of normal weight. For individuals with flatter feet, associations have been found suggesting they have more health problems and poorer balance [46]. Much of this work, however, has been cross-sectional and has not examined the precedence of each of these factors. Foot structure is measured using the Foot Posture Index Six-item version (FPI-6), which quantifies the degree to which a foot can be considered to be in a normal or abnormal position [47]. This assessment is taken with the child standing in a relaxed, weight-bearing and static stance posture. The FPI-6 measures (1) talar head palpation; (2) supra- and infra-lateral malleolar curvature; (3) calcaneal frontal plane position; (4) prominence in the region of the talonavicular joint; (5) congruence of the medial longitudinal arch; and (6) abduction/adduction of the forefront on rearfoot. A 5-point scale (−2, −1, 0, 1, 2) is used to score each item, where the negative and positive scores correspond to supinated and pronated postures, respectively, with zero representing a neutral position. The finalized 6-item version has been found to predict 64 % of the variance in static standing posture and 41 % of the variance in midstance posture during normal walking [47].

#### Physical fitness

Both aerobic and anaerobic fitness are assessed. Aerobic fitness is assessed on a treadmill (Valiant, LODE) using a progressive exercise test. The Bruce protocol is used; the multistage test begins with the participant walking slowly for 3 min at 2.7 km/h at 10 % grade [44]. Participants complete the full Bruce protocol as it has been shown to provide a more accurate measure of maximal endurance time (time to exhaustion) in 4- and 5-year-olds than a modified Bruce protocol. To assist with coordination and balance, participants are instructed to hold onto the handrails for the duration of the test. As well, a researcher is positioned directly behind the child to ensure safety. Heart rate is assessed continuously using a monitor (Polar Electro FT1, Kempele, Finland) worn by the child around the chest. As the speed and incline of the treadmill increase (every 3 min), the child is encouraged to stay walking or running on the treadmill for as long as possible. The test is terminated when the participant is no longer able to continue with the increasing speed or incline of the treadmill, or with refusal to continue exercising despite verbal encouragement. On completion of the treadmill test, the child remains seated quietly for 2 min with heart rate being recorded continuously (approximately 5 times/s) during this recovery period. Both time to exhaustion and heart rate recovery (HRR) are used as indices of aerobic fitness [48]. 1 min HRR is calculated as the difference between HR at the end of the test and at 1 min during recovery. Measurements of HRR using a similar protocol have shown to be feasible and reliable in our pilot work [24, 25].

To estimate short-term muscle power (anaerobic fitness), children complete a Wingate anaerobic cycling test using a cycle ergometer (Pediatric Corival, LODE). To determine maximum pedaling speed, the child sprints as fast as they can for approximately 30 s, pedalling only against the internal resistance of the ergometer. After a short rest, the child begins the Wingate test. When the child reaches 80 % of their maximum pedalling speed, the braking force is applied (0.55 N.m.kg-1). During the test, the child is encouraged to keep pedalling as fast as they can for a total of 30 s. Peak power (PP) output is calculated as the highest power output during the test, mean power (MP) is calculated as the average power over the 30 s. Since some participants may find it challenging to complete the full Wingate test, this study will also highlight the first 10 s as a ‘mini-Wingate’. This 10 s modified Wingate test has been shown to be feasible and reliable for preschoolers [24, 25]. MP over the first 10 s is calculated. All power calculations are measured in Watts (W) and will also be normalized to body mass (W/kg). Fatigue rates are measured after 10 s and 30 s using the minimum power output during the first 10 s and 30 s, respectively. Fatigue rate (%) is calculated as [(PP-min power)/PP) ×100].

For a secondary measure of lower body muscle strength, the child also completes a standing long jump. This measure is used in many field-based fitness assessments in young children [49, 50]. The child is asked to jump as far as possible from a standing position using a 2-foot takeoff and 2-foot landing. The child performs at least 3 attempts with the longest distance, measured to the nearest cm used to assess performance.

Flexibility is assessed using the Sit and Reach Test. The child sits on the floor with their feet held flat against the Sit and Reach Box (Figure Finder Flex-Tester, Novel Products Inc.) and reaches as far forward as they can while keeping both legs extended. Flexibility is measured to the nearest 0.5 cm and the better of two measurements is used. The Back-Saver Sit and Reach [51] protocol is also conducted. This is very similar to the traditional sit and reach test, except that only one leg at a time is assessed. A trial is excluded if the extended leg(s) bend(s) or the hands reach unevenly.

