### Data analyses

To evaluate the stability of DCD over time, a straightforward descriptive analysis will be conducted. This will identify children whose scores change over time: those in the pDCD baseline group who, at a later assessment score above the 16^th^ percentile on the M-ABC-2 as well as those children in the control group whose measured performance declines to at or below the 16^th^ percentile, will be identified. At study end, children with 2 or more assessments differing from their baseline group assignment will be considered to have experienced substantial variability in motor proficiency. Depending on the numbers affected, they will either be used to form one or more additional groups in the analysis, or the analysis itself will be altered such that we retain baseline groups, but also model motor coordination as a time-varying characteristic.

To examine the association between DCD and fitness and adiposity, longitudinal growth models will be fitted with fixed effects for gender, baseline age, DCD status, ADHD symptoms (as these measures become available), time, and time by DCD. The outcomes will be total body fat, central body fat, aerobic fitness, and anaerobic fitness. First, these will be modeled as continuous, and then dichotomized at age-appropriate thresholds for overweight/obesity and inactivity, and fit additional models using the logistic link function. The time by group interaction will reveal the direction, magnitude, and significance of any divergence over time between the two groups. If we observe such a divergence, we will test whether it is mediated by physical activity by adding this measure to the above models. Finally, we will test the question of precedence using a distributed lag model in which each outcome is regressed on previous and contemporary measures of the predictors. This analysis will be repeated with a 3-group variable for DCD status that will differentiate among children who score at or below the 5^th^, those who score between the 6^th^ and the 16^th^, and those who score above the 16^th^ percentiles. This will allow us to assess whether the severity of motor impairment is associated with increased risk of poor fitness and overweight/obesity, and whether physical activity is a stronger mediator in the severe motor impairment group.

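### The Wingate fatigue rate does not require the minimum to follow the peak, so the rate, mainly the 10-s one, can score a rise to peak power as fatigue

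*Protocol article*

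**What the plan says.** All the relevant rules are in the Protocol article, Measurements, Physical fitness.

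- Start of the loaded test: "When the child reaches 80 % of their maximum pedalling speed, the braking force is applied".
- Length: "the child is encouraged to keep pedalling as fast as they can for a total of 30 s".
- Peak: "Peak power (PP) output is calculated as the highest power output during the test". No separate peak is defined for the first 10 s.
- Minimum: fatigue is measured at 10 s and at 30 s, "using the minimum power output during the first 10 s and 30 s, respectively".
- Formula, the same for both windows: "Fatigue rate (%) is calculated as [(PP-min power)/PP) ×100".
- Mean power does get a version for the short window: "MP over the first 10 s is calculated".

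The 10-s part of the test is highlighted because some children may struggle to finish 30 s. Under Data analyses, "The outcomes will be total body fat, central body fat, aerobic fitness, and anaerobic fitness". That section does not say which Wingate index represents anaerobic fitness.

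**The concern.** A fatigue rate should measure how far power falls once it has peaked. The stated rule fixes where to look for the minimum but not when it must occur relative to the peak. It also pairs a minimum from the first 10 s with a peak that may lie anywhere in the 30 s.

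The braking load is a torque set per kg of body mass, so at a fixed load power follows cadence. The load goes on below maximum speed and the child then pedals as fast as possible. Power can therefore be lowest at the start and rise from there. In that case the formula returns the size of the rise and labels it fatigue.

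At stake is the meaning of the fatigue rate, above all the 10-s version, which is the one available for children who do not finish the full test. The formula is stated in full, so this is a rule fixed badly and not a detail left to another document.

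**Working it through.** **Inputs from the Protocol article.** Load applied at 80 % of maximum pedalling speed; 30-s test; peak P from the whole test; minimum from the first 10 s or 30 s; rate = (P − min)/P × 100. The article gives no numerical fatigue rate, so there is no figure to reproduce.

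**Assumptions.** The article gives no power-time data, so every profile below is assumed. Power is taken as proportional to cadence. S is power at the start of loading, P the peak, and E the power at the end of the window, with a steady rise and then a steady fall.

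**Formulas.**
- Stated rule, peak inside the window: (P − min(S, E))/P. This is the larger of the pre-peak shortfall and the post-peak decline.
- Stated rule, peak after the window: (P − S)/P, which is all run-up.
- Post-peak decline within the window: (P − E)/P, or 0 if power is still rising when the window ends.

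**10-s rate, S = 80 (percent of maximum speed).**

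| P | E at 10 s | Stated rule | Post-peak decline |
|---|---|---|---|
| 95 | 90 | (95 − 80)/95 = 15.8 % | (95 − 90)/95 = 5.3 % |
| 95 | 85 | (95 − 80)/95 = 15.8 % | (95 − 85)/95 = 10.5 % |
| 90 | 85 | (90 − 80)/90 = 11.1 % | (90 − 85)/90 = 5.6 % |
| 95, reached at 12 s | still rising | (95 − 80)/95 = 15.8 % | 0 % |
| 95 | 70 | (95 − 70)/95 = 26.3 % | 26.3 % |

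The two definitions agree only when power ends the window at or below its starting value.

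**Both windows, power as a share of peak, linear rise and fall.**

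| Start | Time of peak | Power at 30 s | 10-s: stated / ordered | 30-s: stated / ordered |
|---|---|---|---|---|
| 80 % | 5 s | 60 % | 20.0 / 8.0 % | 40.0 / 40.0 % |
| 80 % | 12 s | 60 % | 20.0 / 0.0 % | 40.0 / 40.0 % |
| 80 % | 5 s | 100 % | 20.0 / 0.0 % | 20.0 / 0.0 % |
| 60 % | 5 s | 80 % | 40.0 / 4.0 % | 40.0 / 20.0 % |

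Here, ordered means the peak within the window and the minimum at or after it. In the first row, power at 10 s is 1 − 0.40 × (10 − 5)/(30 − 5) = 0.92, hence 8.0 %.

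With a start at 80 % of peak and a finish at 50 to 80 % of peak, the 30-s rate is the same under both definitions, because the lowest value falls at the end. The 10-s rate differs in every such profile with a peak at 3 to 20 s.

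**Bound.** If loaded speed never exceeds the unloaded maximum and does not dip when the load goes on, run-up alone gives at most (100 − 80)/100 = 20 %. A dip on loading could raise this, as in the last row of the second table.

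**The case against.** The best counter-argument is that the start rule already limits the problem. Acceleration up to 80 % of maximum happens before loading, and the trigger is scaled to each child. This stands: it caps the run-up contribution at about 20 % under the assumptions above, but does not remove it. It is also true that the article contains no evidence that loaded cadence climbs to 95 % of maximum or that any child peaks at 12 s. The profiles show what the formula does, not how often it happens.

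A second argument is that no named outcome is shown to be affected. Peak and mean power measure short-term muscle power directly and are untouched, and Data analyses names anaerobic fitness but not fatigue rate. This also stands and limits the weight of the point.

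A reader might infer that children with pDCD, being slower to reach peak speed, would look more fatigable, and that this would show up as a spurious divergence between groups over time. The document does not support that. Time to peak does not enter the formula; when the minimum is the starting value, only the ratio of start to peak matters. A peak of 95 gives 15.8 % whether it comes early (with 90 at 10 s) or at 12 s, and a child who reaches only 90 scores lower, at 11.1 %. The direction could go either way.

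A reader might also add that a child who stops early has a minimum near zero and a rate near 100 %. That low comes after the peak, so it is not an ordering fault. How incomplete tests are scored is a derivation detail that a condensed article may leave to the full protocol.

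**Conclusion.** The point holds as a flaw in a stated derivation rule. The fatigue rate can count a rise in power as fatigue when the window's lowest value precedes the peak, or when the peak falls after 10 s. In the assumed examples starting at 80 % and peaking at 95 % of maximum, it reports 15.8 % where the post-peak decline by 10 s is 5.3 %, 10.5 % or nil. The fault in the formula does not depend on these profiles, but its size and frequency in this cohort do.

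The effect is conditional and falls mainly on the 10-s rate. The 30-s rate is usually unchanged in completers. The index is one of several from the Wingate test and is not named as a modelled outcome. No bias between pDCD and control children, and no spurious group-by-time effect, has been shown. This is a modest measurement-definition point that is cheap to correct.

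**What to change.** Define both rates within their own window and in time order, and apply the definition at all waves:

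- 10-s rate = (highest power in 0–10 s − lowest power at or after that peak, up to 10 s) / that peak × 100.
- 30-s rate = the same, over 0–30 s.
- If the peak is the last value in the window, the post-peak decline is 0. Keep the value, flag the child, and report the number flagged by group. Setting these children to missing could make missingness depend on motor ability.

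The cost is a sentence or two in the derivation rules and a recalculation from the recorded power data, where available; the article does not describe how the traces are stored. The corrected rates will be less comparable with rates derived under the stated formula, so the change of definition should be reported with the results.
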